## Abstract

**Background:**

The prevalence of mental health problems in childhood and adolescence has increased significantly, not least due to the COVID-19 pandemic in Germany and other countries worldwide. Although holistic school interventions to promote mental health and prevent mental health problems are considered promising, there is currently uncertainty about their effectiveness due to evaluation studies with heterogeneous methodological quality. This paper presents the study protocol for the evaluation of the primary school module of MindMatters.

**Methods:**

As part of a universal mental health intervention, the MindMatters primary school module ‘Learning Together with Emotions’ aims to promote social-emotional learning (SEL) in the classroom across five skill areas. In addition to classroom activities, the intervention includes a school development module to help primary schools create structures and processes to maintain and promote mental health. To evaluate the effectiveness of the intervention, a two-arm cluster-randomised controlled trial will be conducted, including schools implementing MindMatters over a 12-month period and a control group with no access to the intervention. Data will be collected before and 18 months after initiation of the intervention. Controlled for baseline conditions, multilevel regression analysis will be used to examine primary intervention outcomes at the pupil level (i.e. reductions in mental and behavioural problems). Further mediation and moderation analyses will examine whether proximal outcomes predict changes in mental health outcomes and whether school-level factors influence the effectiveness of the intervention.

**Discussion:**

This study will contribute to strengthen the evidence base for holistic school (mental) health promotion interventions using a study design with high internal validity. Based on an intervention model, the results will not only provide insights into the relationship between proximal and distal outcomes, but will also allow conclusions to be drawn about how the implementation of the intervention affects its effectiveness. Finally, the findings also address the question of whether improved mental health has a positive effect on primary school pupils’ academic performance.

**Trial registration:**

German Clinical Trials Register DRKS00023762. Registered on 5 January 2021.

**Supplementary Information:**

The online version contains supplementary material available at 10.1186/s13063-023-07731-0.

## Introduction

Although childhood and adolescence are considered comparatively healthy periods of life, especially in industrialised countries, researchers point to an epidemiological shift that places greater emphasis on non-communicable diseases (NCDs) such as mental health problems [1]. Indeed, an analysis of the Global Burden of Disease (GBD) 2015 study revealed that mental disorders were the second leading cause of disability-adjusted life years (DALY) among children aged 5–14 years in America and Europe [2]. A meta-analysis of 41 studies from 27 countries estimated a global pooled prevalence of mental disorders in children and adolescents of 13.4%, with the highest prevalence rates found for anxiety and disruptive disorders [3]. Summarising studies using the General Health Questionnaire (GHQ-12), a recent review found a global prevalence of common mental disorders of 25 to 31% depending on the cut-off value used [4]. However, the mental health of young people has deteriorated since the COVID-19 pandemic. In their recent rapid review, Schlack et al. [5] found evidence of significant increases in the proportion of children and adolescents with lower quality of life, higher levels of stress or more symptoms of specific mental disorders, particularly in the early phase of the pandemic. Results from the German longitudinal COPSY study indicate an increase in overall mental health problems from 18% (pre-pandemic) to 29% (mid-2020) to 31% (early 2021), which remained at a high level in the last wave (end 2021, [6]).

Based on these epidemiological findings, there is a strong need for interventions beginning in early childhood before the onset of mental health problems. Schools have long been identified as a key setting for (mental) health promotion and prevention for several reasons. First, it is argued that because of compulsory schooling, a large proportion of children and adolescents, regardless of their social, economic and cultural backgrounds, can be easily reached by school-based interventions. Second, schools are not only places that provide access to young people; they can also influence pupils’ mental health through environmental factors. Although the scientific evidence is heterogeneous, studies suggest that negative classroom learning environments (e.g. classrooms with fewer material resources and whose teachers receive less respect from colleagues) and low school climate (teacher ratings) are associated with lower mental health of pupils [7, 8]. Third, cross-sectional and longitudinal studies have found associations between key educational outcomes and mental health indicators, suggesting that mental health is an important educational resource. Analyses of large Norwegian longitudinal data show that externalising and internalising problems were associated with reductions in upper secondary school completion ranging from 33 to 54% and that this association remained significant even after controlling for family background and school characteristics [9].

In light of these arguments, a number of comprehensive intervention approaches have been developed that focus not only on individual behaviour change but also on organisational change by strengthening the wider physical and social environment and by targeting not only pupils but also teachers and parents [10–12]. However, the evidence base for these whole-school approaches is still limited and inconsistent. In their Cochrane systematic review, Langford and colleagues [13] found small intervention effects for Health Promoting School interventions on a wide range of outcomes (e.g. BMI, physical activity, fruit and vegetable consumption), but not on mental health. However, in terms of age, this refers to older children, not primary school children. In contrast, Weare and Nind’s [14] review of reviews identified small low-to-moderate effects of school-based interventions on mental health and social, emotional and academic outcomes, with greater effects for interventions with longer duration, a balance of universal and targeted approaches, use of a multimodal/whole-school approach and high implementation fidelity. In addition, findings from a meta-analysis of 45 studies showed small improvements from whole-school interventions on pupils’ social and emotional skills, externalising and internalising symptoms. The heterogeneity of these results may be explained, among other things, by the differences in methodological criteria or the range of interventions included. While the Cochrane review by Langford et al. [13] focused exclusively on cluster-randomised controlled trials examining interventions based on the Health Promoting School approach, all the other reviews also included studies using a quasi-experimental design with a comparison group or other designs. Moreover, the review by Weare and Nind [14] included a wide range of universal and targeted interventions. In terms of school type, there is also a scarcity of evidence for whole-school interventions such as MindMatters, particularly for primary schools. Existing evaluation studies for primary schools focus primarily on behavioural prevention programmes rather than on holistic interventions [15].

In summary, uncertainties remain in the evidence for whole-school approaches to mental health promotion, partly due to weak study designs. MindMatters is a comprehensive German school-based intervention that extends from primary to secondary schools and includes curriculum materials and elements aimed at developing the school ethos and environment, taking into account the wider school environment. Previous German evaluation studies have focused on secondary schools and used a questionnaire‐based pre‐post design. While teachers reported improvements in school quality, pupils were found to have lower levels of psychovegetative complaints and psychological distress after programme implementation [16, 17]. The following paper presents the study protocol for the evaluation of the primary school module of MindMatters.

### Aims and hypothesis

The study aims to replicate the intervention effects of MindMatters previously identified for primary schools [16, 17] and to examine the additional effects. Based on a confirmatory multicentre trial, a more rigorous study design will be applied, including a comparable control group. At the pupil level, the focus will be on social-emotional skills, mental health and behavioural problems. In addition to replicating the results at the pupil level, the evaluation aims to examine the changes at the organisational and classroom level, e.g. in terms of improved learning and social climate as perceived by teachers. The study will also examine whether pupils’ academic performance can be improved by strengthening their mental health.

The following hypotheses will be tested:Pupils in intervention schools show higher levels of emotion-related knowledge than pupils in control schools.Pupils in intervention schools have higher levels of social-emotional skills and lower levels of mental health and behavioural problems at post-test compared to pupils in control schools.Teachers in intervention schools report improved diagnostic skills, improved learning and social climate and reduced classroom disruption at post-test compared to teachers in control classes.Parents and teachers of pupils in intervention schools report improved academic performance and learning behaviour compared to parents and class teachers in control schools.Intervention schools with higher implementation quality show greater effectiveness in terms of pupils’ social-emotional skills and mental health, and classroom outcomes such as bullying, classroom climate and disruption, compared to schools with lower implementation quality.

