**Fig. 1 Fig1:**
[figure not shown]
SPIRIT figure

Primary schools are eligible to participate if (1) they are from one of the three federal states (North Rine-Westphalia, Rhineland-Palatinate, Schleswig–Holstein), (2) they have not implemented the MindMatters intervention in the past and (3) they agree to be assigned to either the intervention or control group. After enrolment, eligible schools will be randomly assigned 1:1 to either the intervention or control group using the Microsoft Excel random number function, with randomisation stratified by subgroups: federal state, school size, social gradient and level of activity in school health promotion. Within the subgroups, each school will be assigned a random number, with the proviso that, for example, schools with large random numbers will be assigned to the intervention group and schools with small random numbers will be assigned to the control group. Randomisation and communication with schools will be carried out by the investigators. Schools will be informed individually by e-mail of the outcome of the group allocation. Data will be collected at baseline and again 18 months after the start of the intervention, including the perspectives of pupils and teachers (both baseline and post-test) as well as parents (post-test only). While the MindMatters intervention is implemented in the intervention schools according to defined criteria, no intervention is implemented in the control schools. The trial flow of the evaluation study is shown in Fig. 2. The trial has been approved by the Ethical Review Board of Fulda University of Applied Sciences (Nr. 3.1.9.2), the Ministries of Education in Rhineland-Palatinate and Schleswig–Holstein, and registered with the German Clinical Trials Register (DRKS00023762).

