#### Implementation

In order to assess the quality of implementation of the intervention, each MindMatters lesson or exercise delivered is documented. The documentation includes information on dose (i.e. number of exercises delivered), variation used, fidelity, deviations and preparedness. As a growing body of research suggests that school mental health interventions that expose the whole class to the same content may also have adverse effects [42, 43], teachers are asked to provide open feedback on each lesson. In this way, unintended events (e.g. harmful effects) or deviations are assessed in a non-systematic approach.

In addition to the activities implemented at the curriculum level, teachers from intervention schools are asked to document their school development activities to maintain and promote mental health as defined in the SchoolMatters intervention module (degree of engagement with the SchoolMatters materials, establishment of a school development team, conducting a needs assessment, creating a project plan and a plan for crisis situations, publicity, raising awareness of the intervention within and outside the school) and to assess satisfaction with support and other feedback.

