Statistical analyses will be performed using the latest version of STATA (Stata Corp., College Station, TX, USA). The main analysis will consist of a multilevel regression in which the primary outcomes are predicted at the pupil level using group status (intervention versus control group), controlled for baseline condition. Group status will be included in the model as a fixed effect and a random intercept will be provided for the cluster variables (study region, school, class). Furthermore, all variables with differences between the intervention and control group at baseline will be included in the model. Further mediation analyses will investigate which mediating mechanisms can be identified. It is assumed that the change in mental health outcomes is caused by improvements in proximal (i.e. direct and class/organisational) outcomes. This requires that the group status (i.e. the intervention) is correlated with the proximal outcomes and that the proximal outcomes are significantly related to the distal outcomes. Mediation effects will be examined using the Baron and Kenny partial correlation analysis approach and structural equation models [44, 45]. Moderator analyses will also examine which school-level factors (e.g. size, social gradient) are associated with or influence the impact of MindMatters. Moderator effects are tested using interaction terms in the regression model. The analysis will first be conducted according to the intention-to-treat principle and additionally compared with a per-protocol analysis. Analysis sample 1 includes all those for whom data are available at both measurement points (complete case analysis, as randomised). Analysis sample 2 includes all those reached at baseline (ITT as randomised). Analysis sample 3 includes all those with data available at both measurement points, and schools without intervention are included in the control group. Multiple imputation is used for missing values. To ensure the methodological quality of all analyses, statistical advice is provided by an independent institute.

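### Hypothesis 5 is an observational comparison among intervention schools, yet it is listed with the randomised hypotheses and the abstract words its result causally

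*Protocol article*

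**What the plan says.** **Aims and hypothesis.** The trial is described as confirmatory, and five hypotheses are listed for testing. The fifth reads, in part, "Intervention schools with higher implementation quality show greater effectiveness", with the comparator given as "compared to schools with lower implementation quality". It covers pupils' skills and mental health, and classroom outcomes (bullying, climate, disruption) are included as well. Nothing marks this hypothesis as different in kind from those that compare intervention with control schools.

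**Implementation (under Measures).** "In order to assess the quality of implementation of the intervention, each MindMatters lesson or exercise delivered is documented". For the school development module, "teachers from intervention schools are asked to document their school development activities".

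**Study design.** In the other arm, "no intervention is implemented in the control schools".

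**Data collection, management and statistical analysis.** "Moderator effects are tested using interaction terms in the regression model". The examples of moderators are school size and social gradient.

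**Abstract, Discussion.** The results are expected to allow "conclusions to be drawn about how the implementation of the intervention affects its effectiveness".

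**The concern.** Randomisation protects a comparison between the two arms. It does not protect a comparison between intervention schools that delivered more or better and those that delivered less. The article itself describes delivery as little standardised and left to the needs of each school, and it warns that teachers may find the programme a burden and that classes may stop early. What decides how well a school implements may therefore also decide how its pupils fare.

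H5 inherits the standing of a confirmatory hypothesis, and the abstract promises a causal reading. At stake is the conclusion drawn from it. A positive result could be reported as proof that better delivery produces larger effects, and a null result as proof that delivery does not matter, when either could reflect differences between schools.

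**Working it through.** **1. The plan's own figures.** No sample size or power is given for H5. The stated chain belongs to the two-arm comparison. With assumed rates of 10% and 14% (the article gives only the difference of four percentage points), two-sided 5% and 80% power:

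n per group = (1.960 + 0.842)² × (0.10 × 0.90 + 0.14 × 0.86) / 0.04² = 1033, so 2066 in total.

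2066 × (1 + 14 × 0.01) = 2355, and 2355 / 0.90 = 2617 against 2615 stated. The chain reproduces, but it says nothing about a contrast within one arm.

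**2. Can an interaction term serve H5?** Let g be group (0 or 1) and q implementation quality, in the model 1, g, q, g × q at school level.

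- With q set to 0 in control schools, q and g × q are the same column: rank 3 of 4.
- With q missing in control schools, only intervention schools remain, so g is constant and g × q equals q: rank 2 of 4.
- With a factor that exists in both arms, such as school size: rank 4 of 4, which can be fitted.

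If controls are coded 0 and the duplicate column is dropped, the model runs, but the slope for q equals the slope among the 20 intervention schools alone (0.18687 both ways in a numerical check with simulated data). Control schools add nothing to the estimate of that slope.

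**3. Precision of what remains.** Sample size calculation plans 20 intervention schools. With one value per school and no adjustment:

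- Smallest correlation reaching p < 0.05: t(18) = 2.101, so r = 2.101 / √(2.101² + 18) = 0.44.
- Correlation needed for 80% power: tanh[(1.960 + 0.842) / √17] = 0.59.

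As a second view, split the 20 schools into 10 higher and 10 lower implementers, with 2355 / 40 = 58.9 pupils per school. The design effect is DE = 1 + 57.9 × ICC, and the detectable difference is d = (2.101 + 0.862) × √[2 × DE / (10 × 58.9)]. The last column takes 10% against 14% as an illustration.

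| ICC applied to schools | Detectable d, 80% power | Power for a 4-point difference |
|---|---|---|
| 0.01 (planned) | 0.22 | 36% |
| 0.03 (pilot, lowest) | 0.29 | 23% |
| 0.07 (pilot, highest) | 0.39 | 14% |

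The article assumes effects of d = 0.1 to 0.3 on skills for the whole intervention, so the detectable difference *between* implementers lies in the upper part of that range or above it. Treating the pilot ICCs as school-level values is an assumption. Baseline adjustment would improve these figures and is not counted here.

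**4. What confounding can do.** This is an illustration with assumed inputs: 20 schools, 59 pupils each, ICC 0.05, no causal effect of implementation, and a school trait that explains half of the between-school variance. The share of nominal 5% two-sided tests that reject is:

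| Correlation of implementation with the trait | Rejections |
|---|---|
| 0 | 5% |
| 0.3 | 12% |
| 0.5 | 27% |
| 0.7 | 50% |

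The rates are the same for negative correlations, so the false signal can point either way.

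**The case against.** **A reader might infer that the trial plans an interaction test for H5 that cannot be fitted.** The documents do not support this. Interaction terms are stated for school-level factors, with size and social gradient as examples, and those exist in both arms. Covariates, mediators and moderators does not list MindMatters implementation scores. The rank result shows only that this method is unavailable for H5, not that a planned model will fail.

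**H5 is already worded as a contrast among intervention schools.** That is so, and the contrast can be fitted. What it lacks is randomised protection, and the article does not say so.

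**A reader might take 0.44 and 0.59 as fixed hurdles for H5.** They hold only for an unadjusted analysis with one value per school. Lessons are documented by teachers, so the teaching-module score could be analysed by class, about 174 / 2 = 87 intervention classes if split evenly. That gives more units, but they are still nested in 20 schools and open to the same confounding.

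**A reader might also infer that well-placed schools implement more and so the bias favours the programme.** The direction cannot be known. Materials are used according to need, so more troubled classes might receive more.

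**A condensed article may leave the H5 model to a fuller plan.** Agreed, and the absence of a model is not the complaint. The objection is to what is stated: the unmarked place among confirmatory hypotheses and the causal promise in the abstract. Elsewhere the wording is milder, since the article's own Discussion speaks only of linking fidelity with effectiveness. That makes the abstract easy to align.

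**Conclusion.** The point holds in a limited form. Implementation quality is a post-randomisation measure that exists in one arm only, so H5 is an observational association within the intervention arm, and the abstract's causal wording is not supported by the design. Measured covariates can reduce the confounding but cannot remove it. Precision is low on any reading, though the exact figures depend on the assumptions shown: 20 schools as planned, two-sided 5%, school-level ICCs, and rates of 10% and 14%.

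Neither the primary comparison nor the moderator analyses for factors present in both arms are affected. This should be changed because it alters what the trial may conclude on H5. It does not threaten the main result.

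**What to change.** 1. In Aims and hypothesis, mark H5 as an exploratory, observational association within the intervention arm, separate from the randomised hypotheses.
2. Model it at pupil level with random effects for class and school, adjusted for the baseline outcome and for school characteristics known before randomisation. The stratification factors in Study design supply these: social gradient, size and level of health promotion activity. Teacher-reported classroom outcomes need the same model one level up.
3. Add readiness for change and health-promoting leadership only if their baseline values are used. The article says that both groups provide them but does not say when, and values taken after the start could themselves be affected by the intervention.
4. In the abstract, replace *affects* with *is associated with*.
5. State the low precision, including that class-level scores remain nested in 20 schools.

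An interaction of group with *predicted* implementation, or a complier average causal effect analysis, would use the randomised controls and may be added as sensitivity work. Neither need be required: prediction from 20 schools risks overfitting, and it tests modification by school characteristics rather than by delivered implementation.

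Cost: changes of wording and one model, mostly on data already collected. The price is a weaker stated conclusion for H5 and a few degrees of freedom spent on covariates, which matters with 20 schools and argues for a short, pre-specified list.
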